#### **5.3.1.2 Primary Efficacy Endpoint**

The primary efficacy endpoint is the change in glycated hemoglobin (HbA1c) from baseline to 6 months post-procedure.

### 5.3.2 Secondary Endpoints

The following will be assessed at 1, 3, 6, 12, and 24 months post-procedure compared with baseline:

1. Changes in:

- HbA1c (at 1, 3, 12, and 24 months).
- β-cell function and insulin resistance (HOMA-β and HOMA-IR; formulas provided in the data collection table).
- Mean glucose, postprandial glucose excursions, nocturnal glucose excursions, and time in range (TIR) measured by 14-day continuous glucose monitoring (CGM).
- Lipid profile (triglycerides, total cholesterol, HDL-C, LDL-C).
- Liver function tests (ALT, AST, ALP, GGT).
- Renal function tests (BUN, serum creatinine, eGFR).
- Oral glucose tolerance test (OGTT) and insulin/C-peptide secretion tests (five-point sampling at 0, 30, 60, 90, and 120 minutes), assessed at 6, 12, and 24 months.
- Proportion of subjects achieving HbA1c <7.0% and ≤6.5%.
- Proportion of subjects achieving HbA1c <7.0% without hypoglycemia/severe hypoglycemia or weight gain (composite endpoint).
- Changes in type/dose of antidiabetic medications and proportion of subjects with medication reduction.
- Incidence of hypoglycemia and severe hypoglycemia (blood glucose <3.9 mmol/L).
- Incidence of new-onset significant stenosis (>50%) in the celiac artery, hepatic artery, or branches at 6 months post-procedure, confirmed by digital subtraction angiography (DSA) if CTA indicates abnormalities.
- Incidence of adverse events (AEs) and serious adverse events (SAEs) related to the investigational device and/or procedure at baseline, 7 days (or discharge), 1, 3, 6, 12, and 24 months.
- Incidence of major adverse cardiovascular and cerebrovascular events (3MACE: cardiovascular death, myocardial infarction, ischemic stroke) at 12 and 24 months.
- Changes in quality of life/lifestyle assessment using the EQ-5D-5L questionnaire at baseline and 6 months post-procedure.

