| **Endpoints** | **Primary Endpoints:**   - The occurrence of composite major adverse events (MAE) related to the device and/or the procedure within 30 days post-procedure. MAE includes the following events:  1. Hypoglycemic or hyperglycemic events requiring hospitalization 2. Vascular complications requiring surgical repair, interventional treatment, thrombin injection, or blood transfusion 3. Celiac/hepatic artery dissection or perforation requiring intervention 4. Significant embolic events leading to end-organ damage or requiring intervention to prevent end-organ damage 5. Acute liver dysfunction or liver failure 6. All-cause mortality  - The change in glycated hemoglobin (HbA1c) at 6 months post-procedure compared to baseline levels.   **Secondary endpoints:**   - The changes of Hba1c from baseline at 1, 3, 12 and 24 months post procedure - The changes of assessment of β-cell function and insulin resistance (Homeostatic Model Assessment for β-cell function and insulin resistance, HOMA-β/HOMA-IR) - The changes of mean glucose, postprandial glucose increase, nocturnal glucose increase and time in range (TIR, 3.9-10.3 mmol/L) by 14 - day continuous glucose monitoring (CGM) - The changes of blood lipids (triglycerides, total cholesterol, high- and low-density lipoprotein) - The changes of liver function (alanine aminotransferase, aspartate aminotransferase, alkaline phosphatase and gamma - glutamyl transferase) - The changes of renal function (urea nitrogen, blood creatinine and eGFR) - The changes of glucose, insulin and C - peptide in oral glucose tolerance test (OGTT) - Proportion of patients achieving target HbA1c (< 7.0% and ≤6.5%) - Proportion of patients with HbA1c < 7% without hypoglycemia/severe hypoglycemia or weight gain - Proportion of patients with the changes of in type/dose of antidiabetic drugs - Incidence of hypoglycemia and severe hypoglycemia (blood glucose level < 3.9 mmol/L) - The occurrence of new significant celiac or hepatic artery stenosis at 6 months post procedure (stenosis >50% as assessed by CT angiography and confirmed by digital subtrationsubtraction angiography when CT angiography assessment shows abnormal) - The occurrence of device and/or procedure-related adverse events and serious adverse events - Incidence of cardiovascular and cerebrovascular complications (defined as cardiovascular death, myocardial infarction and ischemic stroke) - Quality of life assessment (EQ-5D-5L) |

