| **Secondary Endpoints** | The following endpoints will be evaluated at 1, 3, 6, 12, and 24 months post-procedure:   1. Changes from baseline at 1, 3, 6, 12, and 24 months in the following parameters:  - HbA1c (at 1, 3, 12, and 24 months) - Assessment of β-cell function and insulin resistance (including HOMA-β and HOMA-IR, formulas provided in Table 5-2, footnote f) - Continuous glucose monitoring (14-day) outcomes: mean glucose, postprandial excursions, nocturnal excursions, and time-in-range (TIR), measured using non-invasive CGM - Lipid profile (triglycerides, total cholesterol, HDL-C, LDL-C) - Liver function tests (ALT, AST, ALP, GGT) - Renal function tests (BUN, serum creatinine, and eGFR, formula provided in Table 5-2, footnote c)  1. Oral glucose tolerance test (OGTT) and insulin and C-peptide release test (5-point sampling at 0, 30, 60, 90, 120 minutes): changes from baseline at 6, 12, and 24 months. 2. Proportion of patients achieving HbA1c targets (<7.0% and ≤6.5%). 3. Composite endpoint: proportion of patients achieving HbA1c <7.0% without hypoglycemia/severe hypoglycemia or weight gain 4. Changes in types/dosages of antidiabetic medications and proportion of patients with dose reduction. 5. Incidence of hypoglycemia and severe hypoglycemia (blood glucose <3.9 mmol/L). 6. Incidence of new-onset significant stenosis (>50%) of the celiac trunk, hepatic artery, or branches at 6 months post-procedure, confirmed by digital subtraction angiography (DSA) in cases with abnormal CTA findings. 7. Incidence of adverse events (AEs) and serious adverse events (SAEs) related to the investigational device and/or baseline procedure, occurring during the baseline procedure, 7 days/discharge, and at 1, 3, 6, 12, and 24 months post-procedure. 8. Incidence of major cardiovascular and cerebrovascular events (3MACE) at 12 and 24 months, defined as cardiovascular death, myocardial infarction, and ischemic stroke. 9. Quality of life and lifestyle assessment at baseline and 6 months post-procedure, including the EuroQol 5-Dimension 5-Level Questionnaire (EQ-5D-5L). |
| **Additional Exploratory Endpoints** | - Body weight and BMI - Waist circumference and waist-to-hip ratio - Office blood pressure - Heart rate variability (Holter) - Catecholamine levels (epinephrine, norepinephrine) - Device performance evaluation (investigator feedback) |

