a. Subjects taking α-glucosidase inhibitors during screening require a 2-week washout period before enrollment.

b. All follow-up visits are calculated from the date of the baseline procedure.

c. Renal function includes BUN, serum creatinine, and eGFR (calculated using CKD-EPI formula).

d. OGTT: 5-point sampling (0, 30, 60, 90, 120 minutes) with glucose, insulin, and C-peptide measurement; indices include Matsuda Index, insulin clearance, insulinogenic index, C-peptide index, late insulin response, and oral disposition index.

e. 14-day CGM for mean glucose, postprandial excursions, nocturnal excursions, and time-in-range (TIR).

f. β-cell function and insulin resistance assessed using HOMA-β and HOMA-IR. HOMA-β = 20 × FINS / (FBG – 3.5); HOMA-IR = (FBG × FINS) / 22.5. (FINS = fasting insulin μU/mL, FBG = fasting glucose mmol/L).

g. Lipid profile includes TG, TC, HDL-C, LDL-C.

h. Liver function tests include ALT, AST, ALP, TBil, GGT.

i. Catecholamines include norepinephrine and epinephrine.

j. HRV evaluated by 24-hour Holter monitoring.

k. Screening CTA of the celiac trunk excludes vascular abnormalities.

l. Pre-EDN angiography excludes vascular anomalies; at 6 months, DSA required if CTA suggests >50% stenosis; no DSA if CTA is normal.

m. Device and procedural information collected for device performance evaluation.

n. Includes major adverse events (MAE), major adverse cardiovascular and cerebrovascular events (3MACE), and hypo-/hyperglycemia.

o. HbA1c results within 1 month prior to screening are acceptable.

p. HbA1c results within 14 days prior to baseline procedure are acceptable; otherwise, repeat testing required.

q. Baseline CGM within 20 days prior to procedure is acceptable; follow-up CGM initiated at visit.

Laboratory tests in this trial include:

- CBC: WBC, RBC, LY, NEU, HCT, Hb, PLT

- Pregnancy test

- Renal function: BUN, SCr, eGFR

- Coagulation profile: PT, APTT, TT, FIB, INR

- Fasting glucose, fasting insulin, fasting C-peptide

- OGTT

- HbA1c

- Lipid profile: TC, HDL-C, LDL-C, TG

- Liver function: ALP, ALT, AST, TBil, GGT

- Catecholamines: norepinephrine, epinephrine

| **Test Item** | **Screening** | **Baseline (≤14 days pre-procedure)** | **Post-op 7 days or discharge** | **Post-op 1 month (±7 days)** | **Post-op 3 months (±14 days)** | **Post-op 6 months (±30 days)** | **Post-op 12 months (±30 days)** | **Post-op 24 months (±30 days)** |
| --- | --- | --- | --- | --- | --- | --- | --- | --- |

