| CBC – 3 ml | X |  | X | X | X | X | X | X |
| HbA1c – 3 ml | X |  |  | X | X | X | X | X |
| Renal + Liver function – 5 ml | X |  | X |  | X | X | X | X |
| Coagulation – 3 ml | X |  |  |  |  |  |  |  |
| Pregnancy test – 5 ml |  | X |  |  |  |  |  |  |
| Lipid profile – 5 ml |  | X |  |  | X | X | X | X |
| OGTT + Insulin + C-peptide – 42.5 ml (3.5 ml for glucose each time point, 5 ml for insulin + C-peptide) |  | X |  |  |  | X | X | X |
| Fasting insulin – 5 ml |  |  |  | X | X |  |  |  |
| Fasting glucose – 3.5 ml |  |  |  | X | X |  |  |  |
| Catecholamines – 5 ml |  | X |  | X | X | X | X | X |

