### 5.4.9 Post-op Day 7 or Before Discharge

All enrolled subjects must undergo CBC and renal/liver function testing at Day 7 post-procedure or before discharge (whichever comes first). Concomitant use of antidiabetics, insulin, and anticoagulants/antiplatelets must be documented. AE/ADE/SAE/SADE and device deficiencies must also be assessed and recorded.

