### 5.4.10 30-Day Follow-up (±7 days)

At 30 days post-procedure, subjects must return for follow-up including:

- Physical exam (height, weight, waist & hip circumference, office BP).
- Antidiabetic medication/insulin use.
- Other treatments (cardiovascular, anticoagulant, antiplatelet therapies).
- Laboratory tests: CBC, renal function (BUN, creatinine, eGFR), fasting glucose & insulin, 14-day CGM, HbA1c, HOMA-IR & HOMA-β, lipid profile, liver function (ALT, AST, ALP, TBil, GGT), plasma catecholamines.
- HRV: 24-hour Holter monitoring.
- AE assessment and management (AE, SAE, SADE, UADE, USADE, ADE).

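### The liver and renal laboratory endpoints leave out the mandatory Day 7/discharge panel, the liver endpoint leaves out total bilirubin, and the blood-draw table drops the 1-month renal/liver and lipid draws

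*Protocol*

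**What the plan says.** **Endpoint times.** Section 5.3.2 opens with "The following will be assessed at 1, 3, 6, 12, and 24 months post-procedure compared with baseline", and the second synopsis has "Changes from baseline at 1, 3, 6, 12, and 24 months in the following parameters". The liver and renal tests stand under these lines. The first synopsis (headed Clinical Study Protocol Synopsis) names the same tests but gives them no visit times.

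**Endpoint analytes.** Section 5.3.2 lists "Liver function tests (ALT, AST, ALP, GGT". The first synopsis lists "The changes of liver function (alanine aminotransferase, aspartate aminotransferase, alkaline phosphatase and gamma - glutamyl transferase". The second synopsis names the same four. None of the three includes total bilirubin, and section 5.3.3 (Additional Assessments) adds neither bilirubin nor an early time point.

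**What is collected.** Section 5.4.9 states: "All enrolled subjects must undergo CBC and renal/liver function testing at Day 7 post-procedure or before discharge (whichever comes first". Note h of the Table 5-2 Clinical Data Collection Schedule defines the panel: "Liver function tests include ALT, AST, ALP, TBil, GGT". Section 5.4.10 schedules the 30-day panel with "liver function (ALT, AST, ALP, TBil, GGT), plasma catecholamines".

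**The blood-draw table.** This table follows the notes to the data collection schedule. Its row "Renal + Liver function – 5 ml" is marked at screening, Day 7/discharge and 3, 6, 12 and 24 months; the 1-month cell is blank. The lipid row is also blank at 1 month.

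**The concern.** The protocol itself fixes both the timing and the content of its laboratory endpoints, and in doing so passes over the panel drawn closest to the intervention. Ablation is in the celiac trunk and hepatic arteries, and contrast is given at the same session. Section 9.2 lists hepatic dysfunction as a potential device or EDN risk, and section 9.1 lists renal impairment as a risk of endovascular procedures. A liver or renal value that rises in the first days and has settled by the 30-day visit cannot appear in a change measured from 1 month on. Bilirubin would not appear in the liver endpoint at any visit.

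The blank 1-month cell matters for a related reason. The 30-day visit closes the primary safety window and is also the first time point of the liver and renal endpoints. A site that drew blood by that table would have no liver panel there.

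**Working it through.** This is mainly a comparison of places in the protocol.

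1. **Panels.** The data collection schedule marks renal and liver function after the procedure at Day 7/discharge, 30 days, and 3, 6, 12 and 24 months, which is 6 panels. Section 5.3.2 uses 1, 3, 6, 12 and 24 months, which is 5. The difference is 6 − 5 = 1, and it is the earliest panel.
2. **Liver analytes.** Collected: ALT, AST, ALP, TBil, GGT = 5. In the endpoint: ALT, AST, ALP, GGT = 4. The difference is 5 − 4 = 1, total bilirubin.
3. **Contrast within section 5.3.2.** The item on related AEs and SAEs names 7 days (or discharge) as an assessment time. The laboratory items in the same section do not, so the Day 7 panel cannot be read into them.
4. **Reference value.** Section 5.3.2 compares with baseline, but before the procedure the liver and renal tests are scheduled only at screening (data collection schedule; section 5.4.6). They are absent from the baseline period in section 5.4.7. The only pre-procedure value to compare with is the screening draw.
5. **Why a count and not only a mean.** Section 6.4 compares continuous outcomes by paired mean differences. As an illustration of the arithmetic only, suppose one of 30 patients rises by 3×ULN at Day 7 and is back at the starting value by 30 days. The 1-month mean change moves by 0. A Day 7 mean change would move by 3/30 = 0.10×ULN. Even with the early time point added, a mean would barely show that patient; a patient count would.
6. **The blood-draw table.** With a blank 1-month cell, the next renal/liver draw after Day 7/discharge is at 3 months (±14 days). Taking 3 months as 90 days, that is Day 90 − 14 = 76 to Day 90 + 14 = 104. The gap from Day 7 is at least 76 − 7 = 69 days, and longer if discharge was earlier. Under the data collection schedule and section 5.4.10 the draw falls at 30 ± 7, Days 23 to 37. The lipid row has the same conflict, and lipids at 1 month are also an endpoint in section 5.3.2.

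**The case against.** The strongest reply is that early hepatic harm already has a place in named endpoints. Acute liver injury or failure is a component of the primary safety composite from the procedure to 30 days (section 5.3.1.1), and related AEs and SAEs are assessed at 7 days or discharge (section 5.3.2). Abnormal laboratory findings count as AEs (Table 12-1), all AEs are reportable (section 12.2), and section 5.4.9 pairs the early panel with AE assessment. This stands. A reader might infer from the endpoint list that early liver injury goes unrecorded; the protocol does not support that.

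A reader might also infer that sites have no laboratory cut-off for calling an event. That does not follow either. Section 20.2 refers event definitions to a study-specific Safety Plan and gives central assessment and classification to the sponsor/CRO safety team. That plan is not shown and may hold the cut-offs.

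Third, collecting more than the endpoints use is normal: the blood count is drawn at every post-procedure visit and is in no endpoint list. The liver and renal items may be meant as longer-term metabolic outcomes, given that section 3.2 reports improved liver function in the pilot, and the SAP may add Day 7 summaries. This limits the weight of the point. It does not remove it, because endpoint times and analytes are fixed here and the related-AE endpoint depends on an investigator's judgement of relatedness, which a laboratory summary does not.

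On the blank cells, section 5.4.2 makes the data collection schedule the summary of all required procedures. They are therefore a clerical slip, not evidence that the 1-month panel was never planned.

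**Conclusion.** The point holds as a modest one. The protocol mandates a liver and renal panel at Day 7/discharge, and a liver panel that includes total bilirubin, but its laboratory endpoints exclude both: 1 of 6 post-procedure panels and 1 of 5 liver analytes. It is a gap in objective laboratory reporting, not a loss of safety capture. In addition, the blood-draw table contradicts the schedule at 1 month for renal/liver and lipids. The gap of at least 69 days arises only at a site that follows that table over the data collection schedule and section 5.4.10.

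The conclusion rests on the protocol alone. The protocol gives no frequency for transient early rises, so none is claimed, and the 0.10×ULN figure is an illustration. An SAP or Safety Plan that already reports the early panel would reduce the first part to a wording correction.

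**What to change.** - In section 5.3.2 and the second synopsis, add Day 7/discharge to the times of the liver and renal endpoints.
- Add total bilirubin to the liver endpoint in section 5.3.2 and both synopses.
- Report descriptively the number of patients whose worst value at Day 7/discharge or 30 days is ALT or AST >3×ULN, or total bilirubin >2×ULN. These limits are already in the protocol as exclusion criterion 11 (section 5.2.2). They are eligibility limits reused here, so a patient who met that criterion at screening and later exceeds one has a new finding. Renal results can be given as change, without a cut-off.
- State that the screening draw is the reference for change in liver and renal tests.
- Fill the 1-month renal/liver and lipid cells in the blood-draw table.

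The cost is a few lines of endpoint wording, one small descriptive table and two table cells, all from draws already in the data collection schedule. One limit remains: the early draw is at Day 7 or discharge, whichever is first, so it may precede Day 7 and will miss some transient rises.

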**Table 5-2 Exclusion Criteria**

| **Clinical Exclusion Criteria** | I. Subjects with any of the following medical history or conditions:  1.Type 1 diabetes mellitus, latent autoimmune diabetes in adults (LADA), or any form of secondary diabetes.  2.History of aortic disease (e.g., aneurysm or dissection) or aortic surgery (including prior celiac denervation).  3.Baseline CTA showing aortic aneurysm/dissection, abnormal hepatic artery anatomy, or other vascular abnormalities unsuitable for ablation (e.g., severe tortuosity or stenosis, intraluminal thrombus, unstable plaques, as judged by the investigator).  4.≥2 self-reported or documented episodes of severe hypoglycemia within the past 6 months (defined as hypoglycemia with severe cognitive impairment requiring assistance).  5.≥1 documented episode of hyperglycemic crisis within the past 6 months requiring hospitalization (including diabetic ketoacidosis or hyperosmolar coma).  6.Severe diabetic complications considered unsuitable for enrollment by the investigator (e.g., advanced retinopathy, nephropathy, vasculopathy, neuropathy, or diabetic foot).  7.Major adverse cardiovascular or cerebrovascular event (MACCE) within the past 6 months, including cerebrovascular accident (CVA), transient ischemic attack (TIA), heart failure (NYHA class III–IV), acute myocardial infarction, or unstable angina requiring hospitalization (including history of CABG or coronary stent implantation), as well as uncontrolled or severe arrhythmias.  8.Severe autonomic neuropathy (e.g., orthostatic hypotension, gastroparesis).  9.Uncontrolled severe hypertension (SBP ≥160 mmHg or DBP ≥100 mmHg) or hypotension (BP <90/50 mmHg).  10.Renal insufficiency or history of renal failure with baseline estimated glomerular filtration rate (eGFR) <60 mL/min/1.73 m².  11.Chronic active hepatitis, severe hepatobiliary disease (including cirrhosis), or hepatic insufficiency (ALT and/or AST >3× ULN, or total bilirubin >2× ULN).  12.Acute or chronic pancreatitis during screening or baseline period.  13.Acute systemic infection during screening or baseline period.  14.History of bleeding tendency or coagulopathy (PT, APTT, or INR >2× ULN; platelet count <80×10⁹/L or ≥700×10⁹/L).  15.Active peptic ulcer disease or gastrointestinal bleeding within the past 3 months.  16.Symptomatic cholelithiasis (including gallbladder, extrahepatic bile duct, or intrahepatic bile duct stones) without effective treatment (e.g., cholecystectomy, bile duct stone removal, internal/external drainage).  17.Other endocrine or metabolic disorders, including hyperthyroidism, hypothyroidism, acromegaly, or Cushing’s syndrome.  18.Autoimmune disease.  19.Active or high-risk malignancy, or life expectancy <12 months.  20.Major surgery within the past 3 months.  21.Hemoglobinopathies or hemolytic anemia that may interfere with evaluation of primary endpoints.  22.Psychiatric disorders that preclude compliance with study procedures.  Note: Subjects not meeting inclusion criteria during screening may be rescreened if deemed appropriate by the investigator.  II. Subjects with prior or expected use of the following medications or treatments: 23. GLP-1 receptor agonists, DPP-4 inhibitors, or SGLT-2 inhibitors within 3 months prior to screening. 24. Systemic or intra-articular corticosteroid therapy within 3 months prior to screening (excluding topical, inhaled, or ophthalmic use). 25. Use of weight-loss drugs (e.g., orlistat) or other weight-reducing interventions (e.g., herbal medications, acupuncture, diet therapies) within 3 months prior to screening. 26. History or expectation of undergoing bariatric surgery (e.g., gastrectomy, liposuction). 27. Use of centrally acting sympatholytics or anticonvulsants within 3 months prior to screening or expected during the study. 28. Subjects requiring long-term anticoagulation who cannot undergo perioperative heparin bridging.  III. Subjects with the following conditions: 29. Body weight fluctuation >10% within the past 3 months. 30. Allergy or contraindication to contrast agents that cannot be adequately managed with premedication. 31. Known allergy to the investigational device or trial-related medications. 32. Participation in another clinical study within 3 months prior to enrollment. 33. Planned participation in another drug or device clinical trial within 24 months post-baseline procedure. 34. Pregnant or lactating women, or women planning pregnancy within 2 years (all women of childbearing potential must undergo a pregnancy test within 7 days prior to the baseline procedure). 35. Anticipated major changes in diet or exercise habits during the study period (e.g., due to religious practices, occupational reasons, or weight-loss programs). 36. Irregular day-night schedule (e.g., shift workers). 37. History of alcohol abuse, drug abuse, or substance dependence. 38. Severe blood loss or planned regular transfusion of blood products within 3 months prior to enrollment or during the study. 39. Any other condition judged by the investigator to pose risk to subject safety or significantly interfere with study outcomes. |

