## 5.3 Evaluation Methods

### 5.3.1 Primary Endpoints

#### **5.3.1.1 Primary Safety Endpoint**

The primary safety endpoint is the incidence of composite major adverse events (MAE)* related to the investigational device and/or ablation procedure occurring intraoperatively or within 30 days post-baseline procedure.

- MAE is defined to include the following events:
- Hypoglycemia or hyperglycemia requiring hospitalization.
- Vascular complications requiring surgical repair, interventional treatment, thrombin injection, or blood transfusion.
- Celiac/hepatic artery dissection or perforation requiring intervention.
- Significant embolic events leading to end-organ damage or requiring intervention to prevent end-organ damage.
- Acute liver injury or liver failure.
- All-cause mortality.

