**Anticoagulation**

Standard intraoperative heparinization should be administered, or other anticoagulation selected as clinically appropriate. Intraoperative activated clotting time (ACT) should be maintained at ~250 seconds.

Post-procedure antiplatelet therapy should be continued for at least 1 week post-procedure. Minimum daily maintenance doses: ASA 75 mg/day or clopidogrel 75 mg/day.

Note: To reduce bleeding risk, subjects on long-term anticoagulation should not receive additional antiplatelet therapy.

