## 9.3 Study-Related Risks

In addition to the above, post-EDN antiplatelet therapy may increase bleeding risk. Additional unanticipated procedure-related risks may occur.

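### The endpoint named for cardiovascular and cerebrovascular events counts only ischemic stroke, so a non-fatal hemorrhagic stroke is left out of it at 12 and 24 months

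*Protocol*

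**What the plan says.** The endpoint is defined in three places with the same components. Section 5.3.2 has "Incidence of major adverse cardiovascular and cerebrovascular events (3MACE: cardiovascular death, myocardial infarction, ischemic stroke) at 12 and 24 months". The Clinical Study Protocol Synopsis has "Incidence of cardiovascular and cerebrovascular complications (defined as cardiovascular death, myocardial infarction and ischemic stroke", without time points. The second Protocol Synopsis repeats the list, "defined as cardiovascular death, myocardial infarction, and ischemic stroke", at 12 and 24 months. None of the three limits the endpoint to related events, and no section adds hemorrhagic stroke.

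The primary safety endpoint (Section 5.3.1.1, repeated in Section 6.1) is a different composite. It covers MAEs "related to the investigational device and/or ablation procedure occurring intraoperatively or within 30 days post-baseline procedure". Its six components are glycemic events leading to hospitalization, vascular complications needing one of four listed interventions, celiac or hepatic artery dissection or perforation needing intervention, significant embolic events, acute liver injury or failure, and death from any cause.

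Two other parts of the Protocol give context. Exclusion criterion 7 screens out a recent "Major adverse cardiovascular or cerebrovascular event (MACCE) within the past 6 months, including cerebrovascular accident (CVA), transient ischemic attack (TIA" and other conditions, with no restriction to ischemic events. The periprocedural section calls for antiplatelet monotherapy and intraoperative anticoagulation ("Intraoperative activated clotting time (ACT) should be maintained at ~250 seconds"), with antiplatelet therapy for at least one week afterwards. Section 9.3 accepts that "post-EDN antiplatelet therapy may increase bleeding risk".

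**The concern.** A reader who sees a cardiovascular and cerebrovascular event rate will take it to cover stroke. As defined, the rate leaves out one of the two main stroke types without explanation. A subject could have a disabling intracranial bleed in the 24 months of follow-up and the reported 3MACE incidence could still be zero.

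This is the only predefined endpoint that could count such an event throughout follow-up without a judgement on relatedness. MAE ends at 30 days and requires relatedness; the AE/SAE secondary endpoint also requires relatedness. If 3MACE does not count the event, no other endpoint is certain to.

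**Working it through.** The Protocol states no figure for this endpoint, so there is none to reproduce. The check takes one case, a non-fatal hemorrhagic stroke, through each place where it might be counted.

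**3MACE (Section 5.3.2 and both synopses).** It is not a cardiovascular death, a myocardial infarction or an ischemic stroke. Not counted at any time.

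**MAE (Sections 5.3.1.1 and 6.1).**
- Glycemic, embolic, hepatic, celiac/hepatic arterial and death components: none fits.
- Vascular complications: the term is undefined and is not expressly limited to the access site or target vessel. A bleed that was judged related, fell within 30 days and needed a listed intervention could be argued in, although the plain reading points elsewhere.
- After 30 days this route closes.

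**Related AE/SAE endpoint (Section 5.3.2).** Counted only if judged related to device or procedure. Table 12-2 cuts both ways. An event that cannot be assessed, or for which a weak association cannot be excluded, is rated possibly related. An event explained by another medication may be rated not related, and Section 12.3 assesses relation to antiplatelet therapy separately (Table 12-3). A bleed attributed to the antiplatelet drug might therefore fall outside this endpoint too.

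**Data collection (Section 12.2, Table 12-4).** Reported to the sponsor as an SAE within 24 hours of awareness, whatever its cause.

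So the event is always collected, but may be missing from every predefined endpoint.

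**Size.** Input: n = 30 planned subjects (Section 6.3). Exact (Clopper-Pearson) two-sided 95% limits:
- As defined, 0/30: lower limit 0; upper limit 1 − 0.025^(1/30) = 0.1157, i.e. 11.6%.
- If counted, 1/30 = 3.3%: lower limit 1 − 0.975^(1/30) = 0.0008, i.e. 0.1%; upper limit, the 97.5% point of Beta(2, 29), = 0.1722, i.e. 17.2%.

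**Chance that it matters.** The documents give no hemorrhagic stroke rate, so the 24-month risk p is assumed over a range. The chance of at least one event is 1 − (1 − p)^30:

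| Assumed p | Expected events (30p) | Chance of at least one |
|---|---|---|
| 0.1% | 0.03 | 3.0% |
| 0.5% | 0.15 | 14.0% |
| 1% | 0.30 | 26.0% |
| 2% | 0.60 | 45.5% |

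These risks are for scale only and are not estimates for this population.

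**The case against.** The strongest reply is that nothing is contradicted. The components are the same in all three places and spelled out each time, so a careful reader knows what is counted. The endpoint is secondary and descriptive, no formal hypothesis is set (Section 6.2), and the success criterion in the Clinical Study Protocol Synopsis uses only MAE and HbA1c. The two intervals above overlap almost entirely, and the SAE record would allow the event to be tabulated later. All of this stands and keeps the point small. It does not explain why an endpoint with this name should leave out hemorrhagic stroke.

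Two stronger readings are tempting, and the documents do not support them.

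- **That the definition removes the very stroke type the trial's drugs make more likely.** The required anticoagulation is intraoperative, and antiplatelet monotherapy has a one-week minimum, though it may continue longer. Any added risk would lie mainly around the procedure, when an early bleed would often be rated at least possibly related and so reach the AE/SAE endpoint. Section 9.3 speaks of bleeding in general. Sections 9.1 and 9.2 name access-site, retroperitoneal and arterial bleeding, not intracranial hemorrhage. Eligibility also excludes coagulopathy, blood pressure at or above 160/100 mmHg and age over 65.
- **That exclusion criterion 7 proves the endpoint wrong.** It is a screening list that also takes in TIA, heart failure, unstable angina and arrhythmia. Entry criteria need not mirror an outcome composite, so the criterion is supporting context only.

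**Conclusion.** The point holds as a mismatch between the endpoint's name and its content. A non-fatal hemorrhagic stroke cannot count in 3MACE, cannot count in MAE after 30 days, and reaches another endpoint only through a relatedness judgement or a generous reading of an undefined MAE component. One event would move the reported incidence from 0/30 to 1/30, or 3.3 percentage points. No success criterion or planned hypothesis depends on it.

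The conclusion is limited to non-fatal events: a fatal hemorrhagic stroke would count in MAE if it was related and within 30 days, and probably in 3MACE as a cardiovascular death, a term the Protocol does not define. It assumes 30 subjects and a plain reading of the MAE components. A reader might infer that such strokes would go unrecorded; they would not, because all SAEs are reported. This is a low-priority improvement, worth making because it costs so little.

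**What to change.** In the endpoint lists of the Clinical Study Protocol Synopsis, the Protocol Synopsis and Section 5.3.2, replace ischemic stroke with: stroke (ischemic or hemorrhagic), reported by subtype. Reporting by subtype keeps the ischemic count visible. Nothing need be added about attribution, since the endpoint already carries no relatedness condition. Note n to the Clinical Data Collection Schedule and Section 12.2 refer to 3MACE by name and take on the new definition without edits. If ischemic stroke alone is intended, the alternative is to say why and to name the endpoint accordingly.

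The cost is three wording changes, with no new visit, test or subject and no change to treatment, because the events are already collected as SAEs. The downside for the sponsor is that the reported rate can only stay the same or become less favourable.
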